### Statistical considerations

A systematic search of the literature showed that the occurrence of a relevant bleeding (resulting in shock or requiring blood transfusion or intervention) in patients with a coagulopathy undergoing invasive procedures is 0.1 - 0.8% [17-24]. Hence, it is expected that in 99% of the patients no major bleeding will occur under prophylactic FFP transfusion and that there will be no increase in the incidence of major bleedings in case no prophylactic FFP transfusion is given. Group size calculation is focused on demonstrating non-inferiority. When the sample size in each group is 198, a one-sided Z test with continuity correction (pooled) achieves 80% power to reject the null hypothesis that the proportion of bleeding patients in the experimental group (no FFP transfusion) is 0.04 or higher, i.e. is inferior to the proportion in the control group (FFP transfusion) by a safety margin of 0.03, in favor of the alternative hypothesis that the proportion in the experimental group is non-inferior. It is assumed that the expected difference in proportions is zero and the proportion in the control group is 0.01. The one-sided significance level of the test was targeted at 0.05. Based on our pilot trial, we expect that all included patients are available for evaluation at the end of the study. Therefore, we intend to enroll 200 patients per treatment arm: 400 patients in total.

### Statistical analysis

Baseline assessments and outcome parameters will be summarized using simple descriptive statistics. Variables will be expressed by their mean and standard deviation if normally distributed, if not normally distributed they will be expressed by their medians and interquartile ranges. The main analysis focuses on a comparison between the trial treatment groups of the primary outcome, the occurrence of relevant bleedings (using a binary variable), expressed in a relative risk estimate and absolute risk increase. In case of clinically relevant baseline imbalances, the primary outcome will be additionally analyzed using multivariate Poisson or logistic regression, when appropriate.

Secondary outcome parameters such as coagulation variables, acute lung injury, number of ventilation days and length of ICU stay will be expressed using continuous variables. Minor bleedings, occurrence of acute lung injury and serious adverse events will be expressed as binary variables (any versus none). The secondary outcome parameters will be analyzed using the Chi-square test (including RR estimates), two group t-test or Mann-Whitney test, when appropriate. In all analyses statistical uncertainties will be expressed in 95% confidence limits.

Because of the non-inferiority design of the trial, both an intention to treat analysis as well as a per-protocol analysis will be done.

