### Study end points

The primary outcome of this study will be a procedure-related relevant bleeding, occurring within 24 hours after the procedure. Relevant bleeding is defined using a validated tool (HEME) in the critically ill [14]: overt bleeding with any of the following: a decrease in hemoglobin by more then 2 g/dL (1.2 mmol/L) in the absence of another cause or transfusion of 2 or more units red cells without an increase in hemoglobin or a decrease in systolic blood pressure by more then 20 mmHg, or an increase in heart rate by 20 beats per minute or more, or bleeding at a insertion or wound site requiring an intervention. Interventions to cease bleeding are defined as an extra suture at the insertion site, embolization by an intervention radiologist or any surgical intervention required to stop the bleeding. The primary end point will be assessed by a physician who is blinded for the randomization result at 1 and 24 hours after the intervention.

Secondary endpoints include the occurrence of minor bleeding (e.g. prolonged bleeding at the insertion site or increase in size of subcutaneous hematoma), the development of ALI and circulatory overload. For this purpose the Lung Injury Score will be calculated at 24 hours. This score includes chest radiographic score, hypoxemia score (PaO2/FiO2), positive end expiratory pressure (PEEP) level (cm H_2_O), and respiratory system compliance score when available [15]. According to the definition, circulatory overload can be defined as bilateral edema on chest x-ray and a wedge pressure > 18 mmHg. In patients who will not have a SwanGanz catheter in place, circulatory overload will be defined as pulmonary edema in the presence of at least 3 of the following: positive fluid balance, elevated central venous pressure, a history of heart failure and increase in oxygenation in response to diuretics. Furthermore, the effect of FFP on correction of INR and clotting variables and the effect of FFP transfusion on outcome (duration of mechanical ventilation, length of ICU stay and ICU mortality) will be evaluated.

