## Discussion

Coagulopathy is highly prevalent in critically ill patients. An INR of > 1.5 occurs in 30% of patients and is associated with increased mortality [13]. Risk factors for coagulopathy are sepsis, liver disease, multiple blood transfusions and trauma [13,25]. Coagulopathy results from an imbalance between activation of coagulation and impaired inhibition of coagulation and fibrinolysis. The disturbance between these components of the coagulation system leads to a variable clinical picture, ranging from patients with an increased bleeding tendency ("consumption coagulopathy") to those with diffuse intravascular coagulation (DIC) with (micro-) vascular thrombosis. However, clinical assessment of coagulation status and bleeding tendency in these patients is complex and the ability of global coagulation tests to accurately reflect *in vivo *coagulation is questioned [26]. In daily clinical practice, the INR, although initially developed to monitor warfarin therapy, is one of the commonly used tests to assess coagulopathy. In ICU patients, the majority indeed has a prolonged INR [10,11,13].

ICU patients frequently undergo invasive procedures, which carry the risk of bleeding. However, the incidence of bleeding after an invasive procedure in patients with a prolonged INR is low. It is shown that central venous catheter placement can be safely done in coagulopathic patients, without the need to correct coagulation abnormalities [19,21]. The incidence of major bleeding, requiring transfusion of red blood cells, ranges from 0.1-0.8%, of minor bleeding from 2.2-6% [20,22,27]. Studies on the safety of performing a percutaneous tracheostomy in patients with a prolonged INR report no evidence of major bleeding [28]. After thoracocentesis, the risk of relevant bleeding is 0.2% and the risk of minor bleeding is 2.6% [29].

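### Ventilation days and ICU stay are set as raw durations tested by t-test or Mann-Whitney, with no account of death, which ends both

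*Protocol article*

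**What the plan says.** The protocol article's Study end points section lists as outcomes "duration of mechanical ventilation, length of ICU stay and ICU mortality". Mortality therefore stands beside the two durations, and no rule connects them.

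The Statistical analysis section sets the scale: "number of ventilation days and length of ICU stay will be expressed using continuous variables". It names the tests for secondary outcomes as Chi-square, "two group t-test or Mann-Whitney test, when appropriate". On analysis sets it says that "both an intention to treat analysis as well as a per-protocol analysis will be done". No survivors-only set is named.

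The article does not say whether a patient who dies on the ventilator or in the ICU contributes the days up to death, is left out, or is ranked worst. It does not mention ventilator-free or ICU-free days, or time to discharge alive.

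**The concern.** Death in the ICU ends both durations. On a raw-days scale a patient who dies on day 2 has a shorter stay than one who leaves alive on day 10, and a t-test or rank test of stay reads that as the better result. The measure mixes fast recovery with fast death.

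This matters in this population and for this question. The Discussion says of the trial's patients that "An INR of > 1.5 occurs in 30% of patients and is associated with increased mortality". The Background puts forward lung injury from plasma, with longer ventilation and ICU stay as its result, and the closing paragraph of the Discussion makes possible harm from plasma one of the trial's aims. These two durations are part of the evidence on that aim. If plasma also raised early mortality, the duration comparison could hide a longer stay in survivors or point the other way.

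**Working it through.** **The plan's own figure.** The article gives no figure for the durations. Its only calculation is for bleeding, where "a one-sided Z test with continuity correction (pooled) achieves 80% power" with 198 per group. Without continuity correction, n = (1.645 + 0.842)² × 2 × 0.01 × 0.99 / 0.03² ≈ 136.0, or 137 after rounding up. The Fleiss correction gives 137/4 × [1 + √(1 + 4/(137 × 0.03))]² = 198.06. The figure reproduces, but it does not bear on this point except through the arm size: "we intend to enroll 200 patients per treatment arm: 400 patients in total".

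**Direction of the bias.** Let m be ICU mortality, and let μS and μD be the mean stay of survivors and of patients who die, taken as equal in the two arms. The mean stay in an arm is (1 − m)μS + mμD. The difference between arms is therefore

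(m₁ − m₀) × (μD − μS).

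It is zero if mortality is equal or if the stays are equal. It favours the higher-mortality arm only when μD < μS, and reverses when μD > μS.

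**Size, on assumed inputs.** None of these comes from the article: survivors' median 10 days, log-normal stay with log-SD 0.8, ICU mortality 25% v 35%, no treatment effect on stay given survival status. Mean = median × exp(0.8²/2) = median × 1.377.

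- Survivors: 13.77 days. Deaths with median 4 days: 5.51 days.
- 25% mortality: 0.75 × 13.77 + 0.25 × 5.51 = 11.7 days.
- 35% mortality: 0.65 × 13.77 + 0.35 × 5.51 = 10.9 days.
- Difference: −0.8 days for the arm with more deaths.

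Varying only the deaths' median stay, with 2,000 simulated trials of 200 per arm:

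| Deaths' median stay | Mean difference, higher minus lower mortality | Significantly shorter in the higher-mortality arm (Mann-Whitney) |
|---|---|---|
| 4 days | 0.10 × (5.51 − 13.77) = −0.83 | 18% |
| 6 days | 0.10 × (8.26 − 13.77) = −0.55 | 9% |
| 8 days | 0.10 × (11.02 − 13.77) = −0.28 | 5% |
| 10 days | 0 | 2.5% (chance, one direction) |
| 14 days | 0.10 × (19.28 − 13.77) = +0.55 | 1% |

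The simulation error at 18% is √(0.18 × 0.82/2000), about 0.9 percentage points.

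**Smaller mortality gaps**, with deaths' median at 4 days: 25% v 30% gives 0.05 × (5.51 − 13.77) = −0.4 days and 7%; 25% v 27% gives −0.2 days and 4%.

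**A second set of assumptions** (survivors' median 8 days, log-SD 0.9, mortality 25% v 35%, rejections counted in either direction) shows the same pattern. With deaths' stay at 0.25, 0.5, 1 and 1.5 times that of survivors, the mean difference is −0.9, −0.7, about 0 and +0.6 days, and Mann-Whitney rejects in 25%, 12%, 5% and 7% of trials. ICU-free days to day 28, with death scored zero, are worse in the higher-mortality arm by about 1.7 to 1.8 days in all four cases, with rejection in 36% to 39%.

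**The case against.** Four points weigh against the concern.

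1. **The article does not say that deaths are kept in as short durations.** A reader might infer this, but it comes from silence. Mann-Whitney with deaths at worst rank would fit the stated wording, and a rule may sit in the full protocol or the SAP, which are not shown. This stands as a limit on the wording. It does not remove the point, because the article itself chooses raw days as the outcome and names the tests. Free days or time to discharge alive would be different outcomes, and an analysis that keeps to the article as written inherits the problem.
2. **It would be too much to say that the arm with more deaths looks better.** That needs a mortality difference and deaths that come before survivors' discharge. The article reports neither, and it claims lung injury and longer stay from plasma, not excess deaths. This stands.
3. **The illustration gives plasma no effect on survivors' stay**, although the harm hypothesis is that it lengthens stay. In the 4-day case a stay about 8% longer in the plasma arm (11.71/10.88 = 1.076) would cancel the mean shift. This also stands. But two harms that cancel to no difference would still mislead.
4. **ICU mortality, lung injury, circulatory overload and serious adverse events are assessed as well**, so a large mortality gap would be visible. This is correct, and it means that the harm question does not rest on the durations alone. Reporting mortality separately does not correct the duration comparison.

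**Conclusion.** The point holds in a conditional form. The article fixes two secondary outcomes as raw durations with simple two-group tests and gives no account of death in patients it describes as having raised mortality. On the plain reading the comparison mixes recovery with death, and its direction depends on when deaths occur.

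Under the assumed inputs, with mortality 25% v 35%, the false signal of a shorter stay runs from about 18% of trials (deaths' median 4 days) through 9% and 5% to chance at 10 days, and the mean difference reverses beyond that. Smaller mortality gaps bring it close to chance. All of this rests on assumed mortality and stays, since the article gives none.

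A reader might go further and conclude that the trial's harm question will be answered wrongly, or that its main result is in doubt. The document does not support either. The primary outcome is bleeding within 24 hours, and its sample size and non-inferiority conclusion are untouched. Other harm outcomes are planned. The change is worth making because these durations feed a stated aim and it costs little.

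**What to change.** State in the analysis plan how death enters both durations. Either of two options would do:

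- Analyse time to extubation (or other end of ventilation, since tracheotomy is one of the study procedures) and time to ICU discharge alive, with ICU death as a competing event, shown as cumulative incidence by arm.
- Keep Mann-Whitney on the durations, with ICU deaths given the worst rank.

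In both cases present the result together with ICU mortality by arm, because a worst-rank difference can come from mortality alone. Report raw ventilation days and ICU stay descriptively, separately for survivors and for patients who died.

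The cost is slightly more analysis work and a summary less familiar to clinical readers than mean or median days. Both options need only the event dates behind the planned durations and the ICU mortality already planned. Ventilator-free and ICU-free days to day 28 are a third possibility, but they would also need vital status after ICU discharge. Sample size and trial procedures do not change.

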### Study organization

The study principal investigator coordinates the study together with the local investigator of the Academic Medical Center. Each participating center has its own local principal investigator who all approved the final trial design and protocol.

This study is considered a low risk trial, in which current practice, transfusion of FFP, with known side effects, is compared to omitting FFP. However, an independent Data and Safety Monitoring Board (DSMB) is instituted and monitors patient safety during the study.

Any serious adverse event (SAE) will be reported to the Institutional Review Board of the Academic Medical Center - University of Amsterdam, Amsterdam, The Netherlands and the DSMB. A predefined list of SAEs will be listed and reported periodically instead of individually, including transfusion reactions and minor bleeding not requiring an intervention.

## Discussion

Coagulopathy is highly prevalent in critically ill patients. An INR of > 1.5 occurs in 30% of patients and is associated with increased mortality [13]. Risk factors for coagulopathy are sepsis, liver disease, multiple blood transfusions and trauma [13,25]. Coagulopathy results from an imbalance between activation of coagulation and impaired inhibition of coagulation and fibrinolysis. The disturbance between these components of the coagulation system leads to a variable clinical picture, ranging from patients with an increased bleeding tendency ("consumption coagulopathy") to those with diffuse intravascular coagulation (DIC) with (micro-) vascular thrombosis. However, clinical assessment of coagulation status and bleeding tendency in these patients is complex and the ability of global coagulation tests to accurately reflect *in vivo *coagulation is questioned [26]. In daily clinical practice, the INR, although initially developed to monitor warfarin therapy, is one of the commonly used tests to assess coagulopathy. In ICU patients, the majority indeed has a prolonged INR [10,11,13].

ICU patients frequently undergo invasive procedures, which carry the risk of bleeding. However, the incidence of bleeding after an invasive procedure in patients with a prolonged INR is low. It is shown that central venous catheter placement can be safely done in coagulopathic patients, without the need to correct coagulation abnormalities [19,21]. The incidence of major bleeding, requiring transfusion of red blood cells, ranges from 0.1-0.8%, of minor bleeding from 2.2-6% [20,22,27]. Studies on the safety of performing a percutaneous tracheostomy in patients with a prolonged INR report no evidence of major bleeding [28]. After thoracocentesis, the risk of relevant bleeding is 0.2% and the risk of minor bleeding is 2.6% [29].

Use of FFP to correct for a deficiency of multiple coagulation factors in case of bleeding [1] is supported by many international guidelines [3,30]. However, efficacy of the use of prophylactic FFP in non-bleeding patients is uncertain [31]. Although consensus regarding profylactic use is lacking, 30-50% of FFP units are administered to non bleeding patients [10,13,32]. There are important variations in ICU clinicians' beliefs and practices in relation to FFP treatment of non-bleeding coagulopathic critically ill patients [12,32,33]. Also, the dose of FFP administered varies widely, ranging from 7.2 to 14.4 ml/kg [32]. Studies on transfusion practice point to the assumption of ICU physicians that FFP corrects clinically relevant coagulopathy, thereby preventing bleeding [34].

FFP can correct a prolonged INR in critically ill patients, but most studies show a reduction and not a complete normalization of INR [1,7,35,36]. A minimally elevated INR (up to 1.5) cannot be corrected, even with higher doses of FFP [37,38]. When INR is > 1.5, a relationship between dose and target INR is found [1,38]. Studies on the dose of FFP to correct INR in ICU patients show conflicting results. Two randomized controlled trials (RCT) in ICU patients have been done. A small study showed that 33 ml/kg was more effective in achieving target levels of coagulation factors compared to 12 ml/kg [1]. However, the range of dosage in this study was wide and an association with bleeding was not studied. In a larger RCT in ICU patients, 20 ml/kg did not differ from 12 ml/kg in correction of INR or increasing coagulation factors above a minimum haemostatic threshold [35]. As complete correction of INR is not a target in this trial, because a mild prolonged INR (< 1.5) is not considered a risk of bleeding [6,37], we chose the dose of 12 ml/kg FFP for the control group. In addition, transfusion with higher doses of FFP is not current practice (own data and [12,32]) and may hamper compliance of physicians to the study protocol.

In recent years, many reports have been published on the detrimental effects of FFP. It is well shown that FFP transfusion is an independent risk factor for new onset of acute lung injury [39-45], in particular in patients who are mechanically ventilated [46]. Furthermore, studies consistently report a significant increase in length of ICU stay [34,44,46].

The TOPIC trial aims to demonstrate that omitting prophylactic FFP transfusion in coagulopathic critically ill patients undergoing an invasive procedure is safe in terms of bleeding complications. Recently, one other trial with similar purposes has been completed (http://www.clinicaltrials.gov NCT00953901), but results have not been published yet. Of note, in this trial, all hospitalized patients were eligible, in contrast to our trial which focuses on ICU patients. Recently, a trial on the effectiveness of FFP in critically ill has been completed (EPICC trial http://www.clinicaltrials.gov NCT00302965), not merely studying the effect of prophylactic FFP use since also active bleeding patients have been included in this study,.

A limitation of our trial is that it is not a double blind placebo controlled trial. However, manufacturing a completely matched placebo was considered not feasible for this non-commercial, academic study. The chosen PROBE design has the advantages of lower costs and greater similarity to standard clinical practice. Furthermore, there is no reason to believe that the reliability of end-point evaluation would differ between a PROBE study and a double-blind study, provided that the same criteria are applied [47]. In addition, it is shown that results from double-blind, placebo-controlled and PROBE trials are statistically comparable [48].

Former studies on the efficacy of FFP have been criticized by using irrelevant end-points, such as correction of INR [6]. The primary outcome of this study will be a procedure-related relevant bleeding, occurring within 24 hours after the procedure as assessed by the HEME tool [14]. A possible disadvantage of the tool is that some items scored with the HEME tool, such as decrease in systolic blood pressure or increase in heart rate, may also occur in the absence of bleeding. However, the inter-rater agreement and agreement between raters on bleeding severity assessments using the HEME tool was shown to be very high (φ = 0.99 (95% CI 0.97-0.99 and φ = 0.98 (95% CI 0.96-0.99 respectively) [14].

In conclusion, the TOPIC trial is a multi-center randomized trial, powered to test the hypothesis that omitting prophylactic FFP prior an intervention in critically ill patients with a coagulopathy is safe and is not associated with increased bleeding complications. In addition, the TOPIC trial determines the effect of FFP on correction of coagulopathy and evaluates the potential detrimental effects of FFP in this patient group.

## Trial status

The trial is currently ongoing; we expect to complete patient recruitment in 2013.

## List of abbreviations

ALI: Acute Lung Injury; APACHE IV: Acute Physiology And Chronic Health Evaluation IV score; CI: Confidence Interval; DSMB: Data Safety Monitoring Board; FFP: Fresh Frozen Plasma; HEME: HEmorrhage MEasurement; ICU: Intensive Care Unit; INR: International Normalized Ratio; PDMS: Patient Data Monitoring System; PROBE: Prospective Randomized Open-label Blinded-End point; RCT: Randomized Controlled Trial; RR: Relative Risk; SAE: Serious Adverse Event; SOFA: Sequential Organ Failure Assessment; TISS: Therapeutic Intervention Score System;
